### Economic evaluation

Following standard practice, we will measure costs for each of the 16 combinations on a per-person basis using an activity-based approach. Costs of the interventions include all program costs, such as YSA savings match, costs for the FLT workshops, Suubi Cartoon, engagement with role models, training, volunteers and donated materials, and running the programs. Research costs are excluded. Costs will be divided by effects to determine efficiency in CEA. To compare the value of two mutually exclusive approaches, a typical RCT reports the cost per added gain as the incremental cost-effectiveness ratio (ICER = (C1-C0)/(E1-E0)), where C=cost, E=effect, 1=intervention, and 0=baseline. The ICER is often compared to other such estimates in the literature and to a decision-maker’s threshold of acceptability to guide policy. For MOST and the factorial design, CEA decisions and optimization are more complex [146]. First, we will test whether any of the 4 components have interacting costs or effects—i.e., economies or effects of scale (If there are no significant interactions, decisions to adopt each of the combinations can be made independently). Next, interventions will be ordered by increasing cost, and we eliminate any “dominated” combinations which are more costly but less effective than a cheaper strategy. Finally, we will compute ICERs for comparison to the literature (such as our past studies [77, 78]) and for assessment as policy options, such as comparing to pre-exposure prophylaxis. Our baseline CEA will focus on ICERs with no budgetary threshold. Next, we will use the MOST framework to assess ICERs while placing constraints on affordability and scalability to select the best possible combination for various levels of a decision-maker’s preferences for affordability and scalability alongside efficiency. Confidence intervals will be generated using bootstrapping and Monte Carlo simulations.

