Factorial designs are innovative in their ability to estimate how two or more components interact, which is not possible with a multi-component packaged intervention. Following the MOST framework, α will be set to 0.10 for all interaction effects, which is justified by the decision-priority perspective [141] guiding this study. To enhance rigor, we will test if interactions among components yield additive and/or synergistic interactions. Additional exploratory analyses will add sex as a covariate and extend each of the previously-described analyses to include interactions of each effect with sex. We propose the following hypotheses for the mediation analyses (also depicted in conceptual model, Fig. 2).

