### Determining the Optimized Intervention

The operational definition of an optimized intervention is one that produces the most cost-effective outcome while meeting the optimization objective, the most cost-effective outcome under our pre-defined real-world constraints (i.e., efficiency, affordability, and scalability). Within the MOST framework, there are two key perspectives to how determine optimization. First, in a *conclusion-priority perspective*, optimization is based solely on the statistical significance at *p* < 0.05 of each component (rejection of the null hypothesis) [141]. However, if a component or an interaction effect failed to reject the null hypothesis, it is not known whether that component or that interaction genuinely had an effect on viral suppression or if a Type II error (incorrect rejection) was made. This perspective (i.e., *p* must be less than 0.05 alone) may erroneously suggest that one or more components should not be included in the optimized intervention. In a *decision-priority perspective* [141], the components and interactions that evidence a statistically significant effect may or may not be included in the optimized intervention as their inclusion depends on the optimization objective – most cost-effective outcome under our pre-defined real-world constraints (i.e., efficiency, affordability, and scalability). For example, our primary analysis will identify the combination of components that produce the greatest odds for sustained viral suppression at *p* < 0.05. However, regarding optimization, if the difference in the odds between having 3 and 4 components is 5%, we could evaluate whether that difference is worth the burden, time, or cost to implement the fourth component. Or, three components could synergistically interact and produce an effect equivalent to having all four components delivered. In a decision-priority perspective, optimization does not have to be based on statistical significance alone but on identifying the costs, effect sizes, and feedback from staff and investigators on the best number of components for sustained viral suppression among ALHIV.

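### The economic evaluation treats non-significant interactions as independence, although the protocol itself calls such results undetermined and the interaction tests have low power

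*Protocol article*

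**What the plan says.** The Economic evaluation section sets out an order of steps. First, "we will test whether any of the 4 components have interacting costs or effects". A bracketed sentence then gives the consequence of a negative result: "If there are no significant interactions, decisions to adopt each of the combinations can be made independently". After that, "Next, interventions will be ordered by increasing cost, and we eliminate any “dominated” combinations", ICERs are computed, and affordability and scalability constraints are applied. Intervals come from bootstrapping and Monte Carlo simulation.

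Two other places bear on the rule:

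- Data analysis plans sets the test level, "α will be set to 0.10 for all interaction effects", and justifies it by the decision-priority perspective.
- Determining the Optimized Intervention says of non-significance that "if a component or an interaction effect failed to reject the null hypothesis, it is not known" whether there was truly no effect or a Type II error. It goes on to say that, under the decision-priority perspective, "optimization does not have to be based on statistical significance alone".

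The Power analysis section gives a minimum detectable main effect (odds ratio 1.77, 14 points) but no power for interactions. The scale of the interaction test in the economic evaluation is not stated.

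**The concern.** The rule makes a significance test the gate to a simpler decision. If the gate shows nothing, each component may be judged on its own. That is the inference which the section on the optimized intervention warns against, and it is applied where the package is chosen, because the optimization objective is defined by cost-effectiveness.

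Two things are at stake. First, a component that adds little or nothing once another is present could be taken as independent because the test missed the antagonism. Second, independence on the scale of the test need not be independence on the scale of the ICER, which divides added cost by added effect. For this trial the natural effect unit is the added proportion with sustained suppression.

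The sentence speaks of combinations. Combinations are mutually exclusive, so I read it as referring to decisions about the components within them.

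**Working it through.** **Inputs.** From Power analysis: base rate 50%, 48 clinics, 576 participants (480 after attrition as stated there), ICC 0.024, main-effect alpha 0.05, power 0.80, odds ratio 1.77. From Data analysis plans: alpha 0.10 for interactions. Assumed: two-sided tests, and two components with odds ratio 1.77 each while the other two are inert.

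**Step 1. Reproduce the protocol's figure.**
- N = 480 gives 10 per clinic. Design effect = 1 + (10 − 1) × 0.024 = 1.216.
- Effective n per level of a component = 240 / 1.216 = 197.4.
- An odds ratio of 1.77 from 0.50 gives 1.77 / 2.77 = 0.639, a difference of 13.9 points.
- A two-proportion test has power 0.799, and the odds ratio giving 0.80 is 1.772. The stated 1.77 and 14 points are reproduced, so the same inputs can be used for interactions.

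**Step 2. Power of the interaction gate.** An interaction compares four cells of 120 / 1.216 = 98.7 effective participants. At N = 576 the design effect is 1.264 and each cell has 144 / 1.264 = 113.9.

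- Logit scale: SE = √Σ 1/(n p(1 − p)), z = |ln(ratio of odds ratios)| / SE.
- Risk-difference scale: SE = √Σ p(1 − p)/n, z = |difference in differences| / SE.
- Power = Φ(z − 1.645) + Φ(−z − 1.645).

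*Full cancellation* (cells 0.500, 0.639, 0.639, 0.639; log ratio = −ln 1.77 = −0.571; difference in differences −13.9 points):

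| N | SE, logit | Power, logit | SE, risk difference | Power, risk difference |
|---|---|---|---|---|
| 480 | 0.415 | 0.40 | 0.098 | 0.41 |
| 576 | 0.386 | 0.43 | 0.091 | 0.45 |

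*Second component's log odds ratio halved* (last cell 0.702; log ratio −0.285; difference in differences −7.6 points):

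| N | Power, logit | Power, risk difference |
|---|---|---|
| 480 | 0.18 | 0.20 |
| 576 | 0.19 | 0.22 |

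A component made wholly redundant by another would therefore pass the gate 55% to 60% of the time.

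**Step 3. Zero interaction on the logit scale.** Let b be the suppression rate with no components. With k components, odds = b/(1 − b) × 1.77^k and the interaction is exactly zero. The fourth ICER relative to the first, at equal cost per component, is the first increment divided by the fourth.

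| b | Suppressed with 0 to 4 components, % | Increments, points | First / fourth |
|---|---|---|---|
| 25% | 25.0, 37.1, 51.1, 64.9, 76.6 | 12.1, 14.0, 13.8, 11.7 | 1.04 |
| 35% | 35.0, 48.8, 62.8, 74.9, 84.1 | 13.8, 14.0, 12.1, 9.2 | 1.5 |
| 50% | 50.0, 63.9, 75.8, 84.7, 90.8 | 13.9, 11.9, 8.9, 6.0 | 2.3 |
| 60% | 60.0, 72.6, 82.5, 89.3, 93.6 | 12.6, 9.8, 6.8, 4.4 | 2.9 |

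The gain from a component thus depends on what is already in the package, by an amount that runs from negligible to nearly threefold.

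**The case against.** The strongest reply is that the sentence is bracketed and permissive, and that the steps after it are unconditional: costs are measured for all 16 combinations, which are then ordered and cleared of dominated options before ICERs are computed. A reader might infer that the plan will produce wrong ICERs. The document does not support that. It nowhere says that ICERs come from main effects alone, and the error arises only if one pooled effect per component is used as its increment in every package. This part of the objection stands. But the later steps need an effect for each combination, and the article does not say that non-significant interactions stay in those estimates. The bracketed rule points the other way.

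Second, the logit scale is inferred from the logistic power calculation and from the mention of odds. The GEE link is not named, and the section on primary outcomes speaks of differences in proportions. A test on the proportion scale would remove Step 3. It would not remove Step 2, where power is about as low on either scale.

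Third, the 2.3-fold ratio is one scenario. If 50% is the rate without a component averaged over the other three, the no-component rate is about 30% and the ratio about 1.25, with the second component adding more than the first. Missing viral loads also count as failure, so with 20% attrition rates above about 80% to 83% are out of reach, which excludes the top cells at 35% (narrowly), 50% and 60%. This is right, and is why only a range is given. Diminishing returns are not a general result.

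Fourth, significance is not the only determinant, since costs, effect sizes and staff feedback also count. That limits the damage, but it is also the principle that the rule contradicts.

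**Conclusion.** The concern holds in a limited form. The economic evaluation states a rule that treats non-significance as independence, and this contradicts the protocol's own account of a non-significant interaction and its decision-priority perspective. The contradiction is material because the gate is weak: power is about 0.40 to 0.45 for full cancellation of a component and about 0.18 to 0.22 for halving of its log odds ratio. These figures assume two-sided alpha 0.10, a 50% base rate, odds ratio 1.77 and ICC 0.024, and they do not depend on the choice between the logit and risk-difference scales.

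The scale argument is conditional. It applies only if the test is on the logit scale, and its size depends on the no-component rate (ratio 1.04 to 2.9 over 25% to 60%). The supportable conclusion is that the rule can lead to misleading decisions about components, not that the ICERs will be wrong. It should be corrected, because it bears on which package is chosen and the correction is cheap.

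**What to change.** Delete the independence sentence. Base adoption on the incremental analysis of all 16 combinations that the Economic evaluation section already outlines, and state that:

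- effects are incremental absolute probabilities of sustained suppression, predicted from the fitted factorial model, set against incremental cost;
- results are shown with and without the two-way interactions, whatever their significance;
- uncertainty comes from a bootstrap that resamples clinics.

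This changes analysis wording only and needs no new data. The downside is wider intervals and a less stable ranking of combinations when interactions are retained, since there are only three clinics per condition (48 / 16). For that reason both versions should be shown, and neither model imposed.

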### Power analysis

Power analyses for our proposed primary analysis was generated using the multilevel logistic regression module for proportions in a 2-level hierarchical design in NCSS PASS 21 [147]. We set the base rate of sustained viral suppression to 50% based on MPI [name]’s Suubi-Adherence study. We assumed *N* = 576 participants recruited from 48 clinics and set α = 0.05, power = 0.80, and the intracluster correlation (ICC) due to clustering of participants within clinics at 0.024 based on data from MPI [name]’s Suubi-Adherence study. We conservatively assumed 20% attrition (*N* = 480). The minimum detectable odds ratio is 1.77, which corresponds to a minimum raw proportion difference of 14% and a standardized effect size of 0.28, which is between a small to medium effect size. For Specific Aim 2, the only difference in power calculations was we set the base rate of sustained viral suppression to 75% and the ICC to 0.038 based on 12-month achieved VL suppression data from MPI [name]’s Suubi-Adherence study. Under these conditions, the minimum detectable indirect effect odds ratio is 1.80, which is between a small and medium effect size [148].

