### Randomization

Aim 1 is a 2^4^ factorial experiment resulting in 16 unique conditions representing all possible combinations of the 4 components. Randomization will be at the level of health clinics (*N* = 48 and geographically distant from each other) to prevent contamination across conditions. Clinics will be randomized to one of the 16 conditions, with 12 ALHIV (aged 11–17 years) enrolled per clinic, yielding main effects and interaction effects for the 4 components on sustained viral suppression (primary outcome) [86]. Refer to Fig. 3 (SPIRIT flow chart).

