### Follow-up plan and tracking

The project will take place in a highly stable region of Uganda where mobility is rare. We will collect telephone numbers, names, addresses, and contact information for three family/friends who know of each participant’s location. We will also be in contact with all participants regularly to determine enrollment and attendance. Moreover, we will have monthly contact with participants across the study conditions through the pill counting (see details above). These procedures will enable our team to continually engage all participants, and minimize loss to follow-up. These strategies were used in our earlier NIH funded studies [2, 53, 55, 56, 63, 65–67, 129–131] including the 6-year *Suubi* + *Adherence* study [104] which yielded a 93.4% retention rate over a 6-year period. Given these numbers and our team’s experience in the study region, we conservatively expect attrition by end of follow-up to be no more than 20%.

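### The power analysis gives N = 480 after 20% attrition from 576, but 20% attrition leaves 461; 480 corresponds to 16.7%, and the effect on power is small

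*Protocol article*

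**What the plan says.** The Power analysis section sets out the enrolled sample: "We assumed *N* = 576 participants recruited from 48 clinics". The Randomization section agrees, "with 12 ALHIV (aged 11–17 years) enrolled per clinic", and 48 × 12 = 576. The allowance for loss follows in the Power analysis section: "We conservatively assumed 20% attrition", with N = 480 in brackets directly after it. The Follow-up plan and tracking section gives the same rate as a ceiling: "we conservatively expect attrition by end of follow-up to be no more than 20" percent.

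The other inputs for the primary outcome are "set α = 0.05, power = 0.80", an intracluster correlation (ICC) of 0.024, and a base rate: "We set the base rate of sustained viral suppression to 50" percent. From these the section reports a minimum detectable odds ratio of 1.77, a difference of 14 percentage points and a standardized effect of 0.28.

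For Aim 2 it says that only the base rate (75%) and the ICC (0.038) differ, and reports a minimum detectable indirect-effect odds ratio of 1.80.

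The Primary outcomes section codes missing viral load and death as not suppressed, so participants without data stay in the denominator.

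**The concern.** The attrition rate and the post-attrition N stand in the same sentence and do not agree. Since 20% also appears in the follow-up section, it looks like the intended planning figure and not a slip for 16.7%. The N that was used is larger than the stated assumption allows, although the allowance is called conservative.

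Two things are at stake. First, if 480 entered the calculation, power is slightly overstated and the minimum detectable effect slightly understated at the attrition the plan assumes. Second, a reader cannot tell whether the 20% or the 480 governs, nor how either relates to a primary analysis that drops nobody.

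**Working it through.** **Attrition**

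- Stated rate: 576 × (1 − 0.20) = 460.8, about 461; per clinic 12 × 0.80 = 9.6.
- Rate implied by 480: 1 − 480/576 = 0.167, or 16.7%; per clinic 480/48 = 10.
- Excess: 480 − 461 = 19 participants.
- Enrolment needed to keep 480 after 20% attrition: 480/0.80 = 600.

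**Which N lies behind the stated effect**

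Inputs from the Power analysis section: base rate 0.50, ICC 0.024, 48 clinics, alpha 0.05, power 0.80. The Data analysis plans section expects equal cells, so each main effect compares 24 clinics with 24. Assumptions made here: two-sided test, normal approximation.

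Formulas:

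- Cluster size m = N/48; design effect DE = 1 + (m − 1) × 0.024.
- Effective number per component level n = (N/2)/DE.
- Unpooled power = Φ(d/SE − 1.96), with d = p2 − 0.50 and SE = √{[0.50 × 0.50 + p2(1 − p2)]/n}. The pooled version uses the pooled standard error for the critical value.

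The plan's figure first. At N = 480: m = 10, DE = 1 + 9 × 0.024 = 1.216, n = 240/1.216 = 197.4. Solving for 80% power gives p2 = 0.638 (unpooled) to 0.639 (pooled), an odds ratio of 1.765 to 1.772, a difference of 13.8 to 13.9 points and a standardized effect (Cohen's h) of 0.280 to 0.282. These match the stated 1.77, 14% and 0.28.

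At N = 461: m = 9.6, DE = 1.206, n = 230.5/1.2065 = 191.0.

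| N | Minimum detectable OR | Difference (points) | Power at OR 1.77 |
|---|---|---|---|
| 480 | 1.765–1.772 | 13.8–13.9 | 79.9–80.4% |
| 461 | 1.781–1.789 | 14.0–14.1 | 78.6–79.1% |
| 576 | 1.70 | 12.9–13.0 | 85.2–85.7% |

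The ranges run over the pooled and unpooled versions. An odds ratio of 1.77 on a 50% base rate means p2 = 1.77/2.77 = 0.639. The loss of power from 480 to 461 is about 1.3 points in either version. A one-sided test at N = 480 gives about 1.66, so the two-sided assumption fits the stated figure.

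**Aim 2**

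The text says that only the base rate and ICC change, so N = 480 carries over by implication. The indirect-effect odds ratio of 1.80 cannot be recomputed, because the article gives no assumptions for the path from component to mediator or from mediator to outcome.

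**The case against.** - **Rounding by clinic.** 480 is also 10 × 48, which is 9.6 per clinic rounded up. That may be the origin; so may dividing 576 by 1.20. The article supports neither over the other. Rounding up is the less conservative direction, and the mismatch with 20% remains.
- **The exact software formula is not given.** This stands in part. With the null variance used throughout, N = 461 gives 1.774, which also rounds to 1.77, while N = 480 gives 1.758. With a t reference on 46 degrees of freedom, 480 gives 1.787 and 461 gives 1.804. That 480 was the input therefore rests on the text naming it and on the two ordinary versions matching there, not on every possible formula. No version makes 480 equal to 20% attrition.
- **461 is not the primary analysis N either.** This is correct. With missing viral load counted as failure, all 576 stay in, and attrition acts on the suppression rates. A reader might infer that the trial will analyse the wrong number of participants; the article does not support that. But 480 fits neither 20% loss nor the analysis described.
- **It hardly matters.** This largely stands. The difference still rounds to 14 points. The 20% is a ceiling, and the earlier study's 93.4% retention would leave about 538 (576 × 0.934).
- **A stronger reading is tempting.** A reader might conclude that the trial is underpowered, or quote about 77% power from a t reference. At N = 461 and 46 degrees of freedom that power is 77.4%, but the same reference already gives 78.7% at N = 480, so the error in N again costs only about 1.3 points. Nor can a shift in the Aim 2 figure be quoted: a direct two-group odds ratio is a different quantity from the stated indirect effect.

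**Conclusion.** The inconsistency is real and minor. Twenty percent attrition from 576 leaves 461, not 480, and the stated odds ratio of 1.77 matches N = 480 under ordinary two-proportion formulas. At the stated attrition, the minimum detectable odds ratio is about 1.78 to 1.79 (about 14.1 points) and power at 1.77 is about 79%, a loss of about 1.3 points. These figures assume two-sided alpha 0.05, a normal approximation, equal allocation by component and equal clinic sizes. They describe an analysis that loses 20% of participants, not the primary analysis, in which missing counts as failure. The effect on the Aim 2 odds ratio of 1.80 is unknown. Nothing here calls the design or the enrolment target into question.

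**What to change.** In the Power analysis section, do one of two things:

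1. Keep 20%, give N = 461 (9.6 per clinic), and restate the primary minimum detectable effect from the same software. It will be about 1.78 to 1.79 on the odds ratio scale.
2. Keep 480 and say that the allowance is 16.7%, with a word on why it differs from the 20% ceiling in the follow-up section.

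In either case, add a sentence saying that the primary analysis keeps all 576 and that attrition lowers the suppression rates rather than N. State whether the 50% base rate already counts missing data as failure. If the first option is taken, rerun the Aim 2 calculation with the corrected N and report its path assumptions.

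The cost is one corrected figure, one or two sentences and a rerun of two calculations. Enrolment, randomization and data collection do not change.

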### Primary outcomes

We are measuring sustained viral suppression, which is a measure of viral load constancy.that is of great clinical and public health importance. Sustained viral suppression is defined as confirmed viral load laboratory tests of < 1000 copies per mL on all 12-, 24-, and 36-month follow-up assessments. Participants who have a viral load laboratory tests of > 1000 copies per mL at any follow-up assessment will be treated as not having sustained viral suppression. In line with another factorial experiment for viral suppression, missing viral load data and deaths will be treated as non-suppression and failure (details below). Participants who are virally suppressed on all 12-, 24-, and 36-month follow-up assessment are coded as 1 for sustained viral suppression. Participants who have missing data or are not virally suppressed on one or more 12-, 24-, or 36-month follow up assessment are coded as 0 for not sustained viral suppression. This handling of missing outcome data allows for calculating the differences in proportions between those who did and did not sustain viral suppression using an intent-to-treat approach [73, 103].

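### The power calculation removes attrited participants, but the primary outcome keeps them and codes them as failures, so 80% power at an odds ratio of 1.77 is not the power of the planned analysis

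*Protocol article*

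**What the plan says.** The Power analysis section gives the inputs for the primary analysis. On the base rate: "We set the base rate of sustained viral suppression to 50" percent, taken from an earlier study by the same team. The sample is "576 participants recruited from 48 clinics", the error rates are "set α = 0.05, power = 0.80", and the ICC is 0.024. On losses: "We conservatively assumed 20% attrition", followed by N = 480. The result is: "The minimum detectable odds ratio is 1.77, which corresponds to a minimum raw proportion difference of 14" percent, with a standardized effect of 0.28.

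The Primary outcomes section fixes how incomplete data enter the outcome: "missing viral load data and deaths will be treated as non-suppression and failure". A participant lacking any one of the three follow-up results is coded 0, and the approach is called intent-to-treat. The Data analysis plans section then fits a GEE to that single binary variable.

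The Follow-up plan and tracking section gives the same loss figure, "we conservatively expect attrition by end of follow-up to be no more than 20" percent, and reports 93.4% retention in the earlier study.

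**The concern.** Deleting a participant and coding a participant as a failure affect power differently. Deletion leaves the two proportions alone and reduces N. Failure coding leaves N alone, lowers both proportions and narrows the difference between them. The power section does the first and the outcome section prescribes the second, yet the power section says its calculation is for the primary analysis.

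This is the only power statement for the four main effects, which are the trial's central aim. The section on determining the optimized intervention itself warns that a null result may be a Type II error. Readers judging a null component therefore need the Type II error rate of the analysis that is run.

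**Working it through.** **Inputs.** From Power analysis: N = 576 in 48 clinics, base rate 50%, odds ratio 1.77, ICC 0.024, α = 0.05, and N = 480 after attrition. From Randomization: "with 12 ALHIV (aged 11–17 years) enrolled per clinic". Each main effect compares 24 with 24 clinics. Two-sided testing is an assumption, because sidedness is not stated; a one-sided test gives 0.876 at N = 480 and does not fit the stated 80%.

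**Formulas.**
- Design effect: DE = 1 + (m − 1) × ICC, with m participants per clinic.
- Effective number per level: n = (N/2)/DE.
- Power = Φ{[(p₂ − p₁) − 1.96·√(2p̄(1 − p̄)/n)] / √([p₁(1 − p₁) + p₂(1 − p₂)]/n)}, where p̄ is the mean of p₁ and p₂ (pooled variance under the null).

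**Step 1: reproduce the stated figure.** An odds ratio of 1.77 on 50% gives p₂ = 1.77/2.77 = 63.9%, a difference of 13.9 points. With N = 480 and m = 480/48 = 10, DE = 1 + 9 × 0.024 = 1.216 and n = 240/1.216 = 197.4. The two standard errors are 0.0498 and 0.0494, so power = Φ[(0.1390 − 1.96 × 0.0498)/0.0494] = 0.799 (0.804 with unpooled variance). Solving for 80% gives an odds ratio of 1.77. The stated figure reproduces, so the protocol did reduce N and leave the 50% unchanged.

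**Step 2: planned coding, with the 50% read as a rate among participants with complete viral loads.** Let d be the share missing at least one result, equal in both levels and unrelated to outcome. The analysed rates are 50% × (1 − d) and 63.9% × (1 − d). N = 576, m = 12, DE = 1 + 11 × 0.024 = 1.264 and n = 288/1.264 = 227.8.

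| d | Analysed rates | Difference | Power, pooled (unpooled) | Minimum OR among those observed, 80% power |
|---|---|---|---|---|
| 5% | 47.5% vs 60.7% | 13.2 points | 0.810 (0.814) | 1.76 |
| 6.6% | 46.7% vs 59.7% | 13.0 points | 0.795 (0.800) | 1.78 |
| 10% | 45.0% vs 57.5% | 12.5 points | 0.763 (0.768) | 1.82 |
| 16.7% | 41.7% vs 53.2% | 11.6 points | 0.698 (0.703) | 1.92 |
| 20% | 40.0% vs 51.1% | 11.1 points | 0.665 (0.669) | 1.97 |

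At 20% missing the odds ratio on the coded outcome falls from 1.77 to 1.57.

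**Step 3: planned coding, with the 50% already counting missing as failure.** No deduction is due. With N = 576 and 50% vs 63.9%, power is 0.852 (0.857 unpooled) and the minimum detectable odds ratio is 1.70, a difference of 13.0 points.

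**Step 4: sensitivity to the ICC.** The ICC after recoding is unknown. For Step 2 at 20% missing, an ICC of 0.010 (assumed) gives 0.721, and 0.038 (the protocol's own value for 12-month suppression) gives 0.615.

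**Step 5: the 480.** 576 × 0.80 = 460.8, so a 20% loss leaves 461. 576/1.2 = 480, which is a loss of 96/576 = 16.7%. With 461 the protocol's own method gives power 0.785 and a minimum odds ratio of 1.79.

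**The case against.** The strongest reply is that the power section calls its 50% a rate of sustained viral suppression, a term the Primary outcomes section defines with missing coded as failure. On that natural reading the cut to 480 is a redundant, cautious deduction, and the trial is better powered than stated. This stands as a possibility. The 50% comes from an earlier study whose coding the protocol does not describe, so the document does not settle it.

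A second reply is that 20% is an upper bound. At the 93.4% retention seen before, Step 2 gives about 80%, the stated power. This also stands, with two limits: the protocol itself plans on 20%, and the outcome needs all three results, so the share coded 0 for missingness can exceed end-of-study attrition.

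A third reply points to the general passage on maximum likelihood and multiple imputation in the section on fidelity monitoring and data quality. It does not displace the explicit rule for the primary outcome.

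A reader might go further and infer that the trial is underpowered, missing a component with the stated effect one time in three, and so likely to drop a useful one. The documents do not support that. The one-in-three figure needs the first reading of the 50% together with the full 20% loss. The section on determining the optimized intervention also bases inclusion on costs, effect sizes and staff feedback, not on significance alone.

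**Conclusion.** The inconsistency is real, and its direction is open. The formula was applied correctly to its inputs, but those inputs describe a completers analysis that the protocol does not plan. At the plan's own 20% attrition, power at an odds ratio of 1.77 is about 67% on one reading of the base rate and about 85% on the other. The corresponding minimum detectable odds ratios are about 1.97 (among those observed) and about 1.70.

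The 67% assumes missingness equal across component levels and unrelated to outcome. If those who drop out would mostly have been unsuppressed anyway, the loss of contrast is smaller. Both figures assume that the ICC stays at 0.024 after recoding. The mismatch between 20% and 480 is a separate small slip that holds on any reading.

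**What to change.** In the Power analysis section:

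1. State whether the 50% base rate counts missing viral loads and deaths as failure.
2. Recompute with N = 576 and 12 per clinic. Multiply both proportions by the expected share with complete viral loads only if the 50% does not already count missing as failure.
3. Restate the power or the minimum detectable odds ratio, with a range over the share missing any of the three results and over the ICC.
4. Remove N = 480 from the primary calculation. If an attrited sample is quoted anywhere, make the percentage and the count agree (20% with 461, or 16.7% with 480).

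The cost is one recalculation and a few reworded sentences. Enrolment, the outcome definition and the GEE analysis stay unchanged. The restated figure may be less or more favourable than 80%, depending on the answer to item 1.
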